#### 2) Itch intensity

In studies 1 and 2, average and maximum itch intensity (base line itch) during the last 24 hours will be assessed by means of a visual analogue scale (VAS 0–10) with the two poles "no itching" (0) and "worst imaginable itching" (10). PSO-patients and healthy skin controls will also be asked to answer an item on the occurrence of chronic itch. In case of PSO-patients, the current itch-intensity in relation to the worst itch-intensity experienced due to PSO will also be assessed. Specifically, participants are asked to indicate whether the current itch is as severe, minimally better, somewhat better, significantly better or much better than the worst itch they have ever experienced due to PSO.

As the application of the suction blister method might induce itch [68–70] and mechanical skin stretching has been shown to increase substance P in the skin of mice [71], we consider maximum induced itch due to the application of the suction blister method as control variable. Itch will therefore be measured by means of a VAS (0–10) every 30 minutes (up to six times) throughout suction blister induction.

### Biologic measures

Material for biological assessments will be obtained by use of the suction blister method. This method was developed more than 50 years ago [65] and allows minimal-invasive ablation of the uppermost layers of the epidermis from the basement membrane separating the epidermis from the dermis. Thereby, blisters form above the basement membrane without injury of the underlying structures during application of a constant negative pressure of 200–300 mmHG. This negative pressure will be applied and controlled by a finely adjustable suction pump (Metzger Technik®, Vaihingen an der Enz: Delta-Typ Labovac, vaccum maximum ≈ -870 mbar), and a plexiglas suction chamber constructed at a workshop of the department of veterinary medicine at the Justus-Liebig-University of Giessen according to the design by [name] based on previous experiences with the method and published methodological protocols [72–74]. It has 3 circular, 8 mm diameter openings as shown in Fig 3, which allow induction of 3 blisters at the same time by applying a negative pressure. In case of PSO-patients, the blisters are induced in such a way that they are located at least 3 cm from the nearest lesional skin area on the supinated forearm of the non-dominant hand side. This process results in the transfer of interstitial fluid and cells from the epidermis and dermis into the blister cavity, including intercellular proteins and other messengers such as neurotransmitters, neuropeptides and cytokines as well as cells of the immune system [75–78].

**Fig 3 pone.0281989.g003:**
[figure not shown]
Illustration of the suction blister methods. A) Suction blister pump (Metzger Technik®, Vaihingen an der Enz: Delta-Typ Labovac, vaccum maximum ≈ -870 mbar) B) three skin blisters containing tissue fluid induced by the use of the suction blister method after three hours.

Blister formation is usually completed after 1–3 hours and the individual duration will be documented. After completion of suction blister induction, the fluid underneath the blister roof is aspirated under sterile conditions from the blister cavity by using an insulin syringe, transferred to an Eppendorf tube (Sarstedt, Nümbrecht: safe seal tube, volume = 1,5ml) and centrifuged to separate cells contained in the fluid from the liquid phase. The supernatant is then stored at -80°C until analysis of the neuroendocrine and immune parameters is performed. For future analyses of mRNA expression, epigenetic methylation patterns or flow cytometry, the cells obtained by centrifugation and the blister roof areal are also collected and stored at -80°C. It is not planned to provoke an immune response prior to suction blister induction as done in other studies [79]. Instead, native material will be collected and stored to examine the in vivo disease conditions and their link with specific social anxiety conditions.

#### 1) Neuroendocrine parameters

Levels of SP will be determined in the blister fluid obtained by use of the suction blister method as described above. Herefore, we will apply ELISA assays (IBL International, Hamburg, Germany) according to modified manufacturer’s recommendations.

#### 2) Inflammatory parameters

IL-6 and IL-17 will be determined by ELISA assay as described above and additional comprehensive panel of mediators of innate and learned immunity might be determined in future studies using Cytometric Bead Array Analysis (Bender MedSystems, eBioscience, Frankfurt, Germany).

### Control variables

In both studies, person-related variables (age, gender, BMI, smoking, use of oral contraceptives, and social status) will be assessed as control variables to control for standard confounding factors. The self-administered patient assessed severity index (SA-PASI) will be used in PSO-patients to measure the severity of PSO during the last 24 hours before examination [80]. In addition, the current psychological health status will be assessed in study 2 with the short form of the German Health Questionnaire for Patients (PHQ-D) [81], and general and current anxiety and depression will be assed with the State-Trait-Anxiety-Depression-Inventory (STADI) [82]. In addition, the suction-blister-pump will be applied during the time from 12 to maximally 3.30pm in order to consider the alteration of neuroendocrine and inflammatory parameters during the day [83–85].

### Statistical analyses

Statistical analyses will be performed using SPSS and the macro PROCESS for SPSS [86–88]. In order to answer research question of study 1, Spearman’s rank-order correlation analyses will be conducted first in order to see which of the control variables are significantly related to itch intensity in PSO patients. These will then be included in step 1 of the subsequent linear hierarchical regression model. Social anxiety measured by the SIAS and SPS will be considered as predictor variable in step 2 of the analyses. Maximum and average itch intensities represent the criterion variables

To answer the research question of study 2, mediation analyses will be conducted using the SPSS macro PROCESS [86–88]. In these analyses, control variables significantly associated with itch intensity as well as social anxiety will be included as possible predictor variables, neuroendocrine and inflammatory parameters as mediators, and average as well as maximum itch intensity as criterion variables. If we find significant correlations between maximum induced itch, and the neuro-inflammatory parameters, we will exploratively conduct a regression analysis with the maximum induced itch as end-point.

Separate analyses will be conducted for patients and controls. To determine the required sample size, we performed an analysis using G*Power [89] to extrapolate the sample size for study 2. Based on correlational studies regarding itch and anxiety [33] as well as on neuroinflammatory parameters and itch [52] in PSO-patients we expect small to medium sized effects (f^2^ = .10). The estimation with an α of 0.05 and a β of 20 revealed that 64 healthy skin controls and 64 PSO-patients are to be included in study 2. Small to moderate effects can be assumed because, on the one hand, only extreme groups are examined and, on the other hand, small to moderate correlations between anxiety and itch intensity (*r* = .179; *p* = .003) have been found in PSO-patients [33] and between neuroinflammatory parameters and itch intensity (*r* = .60; *p* < .01) [52]. In case, that patient recruitment for the studies is slower than anticipated, we would aim to gather additional personnel and material resources to improve the recruitment rate over time. Since study 2 has more strict inclusion and exclusion criteria on e.g. medication and comorbidities than study 1 (see inclusion and exclusion criteria), we expected a reduction in participants who match these premises. In addition, motivational factors are to be considered, as in contrast to study 1, study 2 will be conducted in a laboratory setting. We therefore estimated that n = 500 participants need to be included in study 1 to achieve the calculated sample size of n = 128 participants for study 2. As there is no cut-off value in the user manual of the SIAS [90] to categorize somebody as low socially anxious, we planned to use percent range ≤ 25 in order to categorize 32 participants per group as being low socially anxious. Due to the pandemic situation, participant recruitment during the course of 2020 and 2021 was and still is very difficult. Therefore, we had to change this inclusion criterion for study 2 and now invite all participants of study 1 irrespective of their social anxiety scores to take part in study 2. High and low socially anxious participants will now be identified by median split. Statistical analyses will be conducted when the targeted sample size (study 1: *N* = 500, study 2: *N* = 128) has been achieved or further inclusion of participants is no longer possible due to the end of funding. No intermediate data analysis is planned. Data collection started after ethic approval in December 2020 for study 1 (number of currently assessed patients n = 234; number of currently assessed healthy controls n = 174), and in September 2021 for study 2 (number of currently assessed patients n = 27; number of currently assessed healthy skin controls n = 15). Data collection will be continued until the planed sample sizes are reached or as long as funding is available.

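### Control variables enter the study 2 mediation models on significance with itch, so a confounder of the social anxiety to mediator path is not guaranteed adjustment

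*Protocol article*

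**What the plan says.** Under Control variables, the article states that "person-related variables (age, gender, BMI, smoking, use of oral contraceptives, and social status) will be assessed as control variables to control for standard confounding factors". SA-PASI is added in patients as a measure of severity.

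Under Statistical analyses, entry into the models is conditional. For study 1 the variables are correlated with itch "in order to see which of the control variables are significantly related to itch intensity in PSO patients", and "These will then be included in step 1 of the subsequent linear hierarchical regression model". For study 2 the mediation models take "control variables significantly associated with itch intensity as well as social anxiety will be included as possible predictor variables", with "neuroendocrine and inflammatory parameters as mediators, and average as well as maximum itch intensity as criterion variables". No control variable is entered unconditionally. The same section adds: "Separate analyses will be conducted for patients and controls". With the planned numbers, each mediation analysis therefore has 64 participants.

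The study 2 sentence can be read in two ways:
- Variables associated with itch enter, and social anxiety is listed beside them as the predictor.
- Only variables associated with both itch and social anxiety enter.

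Neither reading mentions association with the mediators.

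**The concern.** A mediation model has at least two kinds of equation: one with each mediator as dependent variable, and one with itch. A variable confounds the path from social anxiety to a mediator (the a-path) if it is related to both of those. Its significance with itch is a different question. BMI or smoking, for example, could be related to both IL-6 and social anxiety but only weakly to itch. Such a variable could fail the screen and drop out of the equation where it matters.

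The article recognises influences on the mediators elsewhere. It restricts the time of sampling because the parameters vary over the day. It also says "we consider maximum induced itch due to the application of the suction blister method as control variable", partly because skin stretching may raise SP. The covariate rule has no such mediator-side criterion.

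At stake is the indirect effect, which is the main result of study 2. An a-path produced by an unadjusted confounder can look like mediation.

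**Working it through.** **Inputs from the article.** 64 patients and 64 controls in study 2, analysed separately; 250 and 250 in study 1; f² = .10, α = .05, β read as 20%; and a cited correlation of .60 between neuroinflammatory parameters and itch. The Introduction describes the source of that .60 as a study in prurigo nodularis, so it is only a loose anchor for psoriasis.

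**Assumed.** All correlations of the confounder with social anxiety, mediator and itch.

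**Step 1: the plan's own figure.** For one regression coefficient, the noncentrality is √(f²·n) = √(.10 × 64) = 2.53. A one-sided 5% t test then has power .804, so n = 64 reproduces. Two-sided, n = 81 would be needed, and 64 gives power .70. Sidedness is a separate matter; n = 64 is used below.

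**Step 2: what passes the screen.** The critical Spearman value is tanh(1.96·√(1.06/(n−3))).
- n = 64: tanh(1.96 × .1318) = .25
- n = 250: tanh(1.96 × .0655) = .13

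The probability of passing for a true correlation of .10, .20 or .30 is 12%, 34% and 65% at n = 64, and 33%, 87% and above 99% at n = 250.

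**Step 3: bias in the a-path.** If the confounder is omitted and there is no true a-path, the standardised bias is r(confounder, anxiety) × r(confounder, mediator). Under the screen it is roughly that product times (1 − probability of entry). For .25 and .40 with 12% entry this is .10 × .88 = .088. For .30 and .50 it is .15 × .88 = .132.

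**Step 4: simulation.** n = 64, 6,000 replicates per row, no true a-path, two-sided 5% Spearman screen against itch, first reading of the study 2 sentence. Joint significance means that both the a-path and the mediator-itch path have p < .05.

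| Confounder with anxiety / mediator | Mediator-itch path | Confounder-itch correlation | Admitted | a-path bias | a-path false positives | False joint significance |
|---|---|---|---|---|---|---|
| .10 / .30 | .60 | .18 | 27% | +.019 | 5.5% | 5.5% |
| .10 / .30 | .30 | .09 | 11% | +.024 | 5.7% | 3.6% |
| .25 / .40 | .60 | .24 | 45% | +.048 | 7.9% | 7.8% |
| .30 / .50 | .60 | .30 | 63% | +.048 | 9.5% | 9.5% |
| .25 / .40 | .25 | .10 | 12% | +.087 | 11.8% | 5.7% |
| .30 / .50 | .20 | .10 | 12% | +.128 | 19.0% | 6.0% |
| .25 / .40 | .60, opposing direct path −.14 | .10 | 12% | +.086 | 11.2% | 11.2% |
| .30 / .50 | .60, opposing direct path −.20 | .10 | 11% | +.133 | 19.8% | 19.5% |

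With the covariate always included, bias is 0 in every row, a-path false positives are 4.4-5.1%, and false joint significance is 1.2-5.0%.

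The second reading admits fewer variables. In a separate run with .30 / .30 and a mediator-itch path of .30, entry fell from 10% to 6% and bias was .080 instead of .077.

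**Step 5: screen carried over from study 1.** With n = 250 for the screen and a mediator-itch path of .60, .25 / .40 is admitted in 96% of samples (bias +.004, false positives 5.4%). The .30 / .50 case is admitted in over 99% (bias +.001, 5.0%).

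**Step 6: study 1 itself.** For a confounder correlated .40 with anxiety, the bias in the itch model at n = 250 is +.005 if its correlation with itch is .20 (86% admitted), and +.02 if it is .10 (32% admitted).

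**The case against.** Several objections have force.

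- **Strength of the link to itch.** If the mediator really correlates .60 with itch, a confounder correlated .40 with the mediator reaches .24 with itch through that route alone, and is admitted in nearly half of samples. A confounder-itch correlation of .10 then needs a much weaker mediator-itch path or an opposing direct path. This stands, and it is why the middle rows of the table belong in the range.
- **The weak end.** With weak confounding, or with a weak mediator-itch path, false joint significance stays near nominal. This stands.
- **Where the screen is run.** The article does not say whether the study 2 screen is rerun at n = 64 or carried over from study 1. It describes the screening step for patients only. A reader might infer a low-powered screen in the same 64 people; the text does not settle that. Since study 2 participants come from study 1, selection is data-driven either way.
- **Design and disclaimers.** Sampling time is restricted, biologicals and psychopharmacological treatment are exclusions, and the Discussion disclaims causal conclusions. These do not address BMI, smoking or age, which the article collects as confounders.
- **SA-PASI.** The Introduction describes a circle linking itch, scratching, stigmatisation and severity, so forcing severity into every model could over-adjust. This stands and shapes the fix.

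A reader might also infer that the rule excludes all confounders of the mediator path. It does not: one that is also clearly related to itch will usually enter. The study 1 rule does not support the mediation point, since study 1 has no mediators.

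**Conclusion.** The concern holds for study 2 in a limited form. The stated rule gives no route into the mediator equations for a control variable that is related to social anxiety and to a mediator but not significantly to itch. Such a variable is not guaranteed entry, although it was collected for adjustment.

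The size cannot be fixed from the article. Under the assumptions shown, a-path bias at n = 64 is about +.02 with a 5-6% false-positive rate for weak confounding. It is about +.05 and 8-10% for moderate confounding with the cited mediator-itch correlation of .60, and +.09 to +.13 and 11-20% when the confounder is only weakly related to itch. False joint significance runs from about 4-6% to about 20%. If the screen is carried over from n = 250 and the mediator-itch correlation is .60, the harm nearly vanishes. Study 1 is affected only slightly, by up to about +.02.

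The documents do not support saying that the indirect effect will be confounded. They do show that the plan does not protect against it, when it easily could.

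**What to change.** Replace the significance screen with one covariate set fixed before analysis, taken from the article's own list: age, gender, BMI, smoking, oral contraceptives where applicable, and social status. Enter it regardless of significance in the mediator equations and the itch equation of study 2, and in step 1 of the study 1 regression. Use the same set for average and maximum itch.

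In patients, report the results with and without SA-PASI, and say that severity may be a confounder or may lie on the pathway. Maximum induced itch arises during sampling and could itself depend on social anxiety, so it is not placed in the fixed set here.

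All these variables are already collected, so the change is one of wording. With one column per variable, the six covariates reduce the residual degrees of freedom of a mediator equation from 64 − 2 = 62 to 64 − 8 = 56; multi-category coding would take a few more. If f² = .10 is the partial effect, one-sided power at n = 64 is .803 with eight predictors, against .804 with one.

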### Neuroendocrine and inflammatory parameters relate to itch and anxiety

There are a number of neuroendocrine and inflammatory parameters interacting with each other, which are related both to the intensity of itch as well as to anxiety. Of these parameters, we consider substance P (SP), IL-6 and IL-17 of special interest. Concerning itch, injected SP was shown to induce it in mice [42, 43], in healthy human controls [44], as well as in PSO-patients [45]. Within this context, it was recently shown that in PSO-patients and in patients with atopic dermatitis, the amount of SP and its neurokinin-1 receptor (NK-1R) receptor was significantly increased in nerve fibers in itchy compared to non-itchy skin of the same patients and to healthy controls [46]. In the same study, gene fold changes of IL-6 and IL-17A were overexpressed in itchy skin of PSO-patients. Of note, SP is capable of liberating IL-6 and IL-17 [47, 48], and IL-17 has also been shown to further release IL-6 [49]. Moreover, higher levels of IL-6 have been found in itchy skin of patients with different diseases. With this respect, it was found that IL-6 concentration were significantly related to scratching behavior after intradermal injections of calcium phosphate in mice. In the same study, in human subjects with chronic kidney disease, IL-6 concentrations were significantly increased in itchy compared to non-itchy skin [50]. In addition, an increased amount of nerve fibers containing IL-6 was found in lesional compared to non-lesional skin of patients with the itchy skin diseases atopic dermatitis and prurigo nodularis [51]. More recently, this finding was supported by a positive relationship between pruritus severity and IL-6 in patients with prurigo nodularis [52]. In addition, IL-17-antagonists were shown to reduce itch in PSO-patients [53–55].

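### The exploratory regression on induced itch is run only after significant correlations in the same data, so its p-values are too small and its effects overstated when true associations are null or weak

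*Protocol article*

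**What the plan says.** The Statistical analyses section gives study 2 mediation models with "average as well as maximum itch intensity as criterion variables". These models do not wait for a prior test of the mediators against itch. The section then adds a side analysis on itch provoked by the suction procedure: "If we find significant correlations between maximum induced itch, and the neuro-inflammatory parameters, we will exploratively conduct a regression analysis", with maximum induced itch as the end-point.

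The text fixes the end-point and the condition. It does not name the predictors, the type of correlation for this step or any multiplicity rule. The Introduction limits the biological parameters to three: "we consider substance P (SP), IL-6 and IL-17 of special interest". The Itch intensity section gives induced itch a different main role: "we consider maximum induced itch due to the application of the suction blister method as control variable". The analyses are split by group: "Separate analyses will be conducted for patients and controls". The planned study 2 size is 64 patients and 64 controls.

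**The concern.** If the regression relates induced itch to the parameters that were just screened against it, the second step largely repeats the first after selection. A nominal 5% level assumes that the analysis would have been run whatever the data showed. Here it is run only when the sample correlations happen to be large, so p-values are too small and coefficients and R² too large, given that the regression appears at all.

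The reverse case matters too. When no correlation is significant, no adjusted estimate with an interval is produced. Induced itch is recorded because suction itself may cause itch, and skin stretching may raise SP. A small coefficient with a narrow interval would be useful evidence that sampling does not disturb the mediators. Non-significance at 64 per group is not that evidence, although it could be read that way.

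**Working it through.** **Inputs from the article.** Three parameters (SP, IL-6, IL-17); two groups analysed separately; n = 64 per group; f² = 0.10, α = 0.05, β given as 20 and read as 20%; a cited anxiety-itch correlation of .179, used here as an example of a weak true effect.

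**Assumptions.** The screen is any of three two-sided Spearman tests at 5%. The regression is ordinary least squares of induced itch on all three parameters. Data are normal, and the parameters correlate 0, .3 or .5 with each other. The article gives none of these, so ranges are shown.

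**The plan's own n.** For one regression coefficient the noncentrality is √(f²·n) = √(0.10 × 64) = √6.4 = 2.53. A one-sided test on 62 df (critical t = 1.67) has power 0.804, so 64 is reproduced. Two-sided, power is 0.70 and n would be 81. The article does not state sidedness; that is a separate matter.

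**How often the screen opens with no true association.**
- Three independent tests: 1 − 0.95³ = 14.3% in one group.
- Six independent tests over both groups: 1 − 0.95⁶ = 26.5%.
- Simulated, one group: 12-15%, depending on how the parameters correlate.

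**What passes.** The Pearson threshold is r = t/√(df + t²) = 1.999/√(62 + 1.999²) = .246, and the Spearman threshold is close to it. No correlation smaller than about .25 can pass, whatever the true value.

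**What the regression then shows** (simulation, 6,000 to 8,000 data sets per setting, n = 64; ranges are over the between-parameter correlations):

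| True r with induced itch | Screen opens | Mean selected correlation | Overall F p < .05, screened / always run | Mean R², screened / always run |
|---|---|---|---|---|
| 0 | 12-15% | .29 (absolute) | 28-33% / 5% | .10-.11 / .05 |
| .179 | 49-61% | .31-.32 | 52-80% / 27-54% | .13-.18 / .09-.14 |
| .30 | 87-96% | .34-.35 | 80-99% / 71-98% | .19-.31 / .17-.30 |

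At a true r of .179 the selected correlations are about .32/.179 = 1.8 times too large. At .30 they are about .35/.30 = 1.2 times too large. At .60, the one parameter-itch correlation that the article cites, the screen practically always opens and no inflation is visible.

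**Single coefficients under the null.** Once the screen is open, a parameter that passed it has p < .05 in the regression in 46-70% of data sets.

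**Whole procedure under the null.** The chance that the screen opens and some coefficient is significant is 6-10% (for example .141 × .709 = .100). Running the regression every time gives at least one significant coefficient in 13-14%.

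**If the predictor were social anxiety instead.** The error rate given an open screen is 5.1% when social anxiety is unrelated to the parameters and 8.7% when it correlates .3 with them.

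**The case against.** The case against is substantial, and most of it narrows the point.

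- **Predictors are not named.** A reader might infer that inflation follows from the rule itself. It does not: it depends on the screened parameters being the predictors. That is the natural reading but not a stated one, and with social anxiety as predictor there is little or no bias. This stands.
- **Nulls are estimated in part.** A reader might infer that a null association is never estimated. The correlations that form the screen are computed in every case, and the article does not say that non-significant ones will be withheld. Only the regression is missing. This stands.
- **Stronger effects.** The article cites r = .60 between neuroinflammatory parameters and itch, and at that size selection does nothing. True, but the plan itself expects small to medium effects (f² = 0.10), where the bias is visible.
- **The conditional rate is not the overall error rate.** The 28-33% applies only to regressions that are run. Over all data sets the screened procedure yields fewer significant coefficients than the unconditional one. This stands. The problem is distorted reporting of what passes, not a higher total of false positives.
- **The step is labelled exploratory.** It is, and induced itch is chiefly a control variable. A reader might infer that the mediation results are compromised; the documents do not support that, since those models use average and maximum itch intensity and are not screened in this way. The label lowers the stakes but does not remove selection from the reported coefficients.

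**Conclusion.** The point holds in a limited form. The rule screens and then re-analyses the same outcome in the same participants. If SP, IL-6 and IL-17 are the predictors, any regression reported under it has too-small p-values and overstated effects when true associations are null or weak. Under the null at n = 64, the F test rejects in about 28-33% of the regressions that are run, and a true r of .179 appears as about .32. At r = .30 the distortion is modest, and for strong correlations it is negligible.

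These figures rest on normal data, a two-sided 5% Spearman screen and all three parameters entered together. They would be worse in a smaller sample. The article lets analysis begin when funding ends; at the numbers assessed when it was written (27 patients, 15 controls), only correlations above about .38 and .51 would pass.

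Neither main research question is affected. The point is minor, but the change is nearly free.

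**What to change.** Delete the condition. State that an exploratory regression of maximum induced itch on SP, IL-6 and IL-17 will be run in each group in every case. Report the overall F test and all three coefficients with 95% CIs, labelled exploratory, together with all the correlations whatever their significance.

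The cost is one changed sentence and one regression per group, with no new data. No intermediate analysis is planned, so the change can be made before the data are analysed. There are two downsides. Null results will have to be reported. And three unadjusted coefficients carry about a 14% chance of at least one false positive per group, more than under the present rule, so they should be read as estimates and the F test used if a single test is wanted.
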